### Recruitment

COPMI-children will be recruited in several ways. First, they can be recruited through, the online Kopstoring program (http://www.kopstoring.nl). This open website has information about the study and its objectives. Second, the mental health institutions who are cooperating in this project and provide the online program give information about the Kopstoring program to potential respondents and can recruit young people through their websites, databases, networks and contacts. General practitioners (GPs) will be informed about the study so they can also preselect eligible respondents. There will also be banners and links created for the internet. Public Relations (PR) will be led by the Trimbos Institute which has experts and experience in the field of recruitment and PR.

### Intervention

The Kopstoring program consists of 8 consecutive online weekly chat group meetings and a ninth evaluation meeting in a chat box at the website http://www.kopstoring.nl. The aim of the intervention is to strengthen protective factors, such as self-management skills and psychological well-being, and prevent the development of psychological disorders. The experts (prevention workers and psychologists from mental health care institutions) involved in the delivery of the intervention are specialized in the field of COPMI-problems and in the prevention of mental health problems in young people. The intervention is protocol-driven and well-structured. There are 8 themes, so each week there is a new theme. The themes are; getting acquainted with the home situation, roles in families, thoughts and feelings, questions about addiction and mental problems, different styles of behaviour, social networks, leading your own life in relation to social networks and what is coming up in the future. The participants are required to carry out homework assignments before entering the chat box (chat room) meeting [18]. The Kopstoring program is part of an informative website which also provides an e-mail service and chat options, alongside the Kopstoring program.

### Care as usual in the Netherlands

The control condition in this trial is a waiting list with unrestricted access to care as usual. Usual care in the Netherlands is a mix of several services. In this study, care as usual is not standardized and there are no protocols. Young people can request a lot of services: for example, a general practitioner, a psychologist, or mental health or institutional services such as counselling sessions.

### Sample Size calculation

The sample size calculation is based on the ability to detect a medium size or larger clinical effect. This corresponds to a standardized mean difference (Cohen's d) of d > 0.45 [19]. We will test the hypotheses at a conventional power of (1 - beta) = 0.80 and alpha = 0.05, 2-tailed (cf. Friedman et al., 1996). For this n = 78 is required per condition, therefore a total of 156 participants. Finally we want to compensate for possible drop-out during the trial. The drop-out rate from the pilot study was 28% [9]. We therefore need to enrol 156/(1-0.28) = 214 participants during the trial.

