**Methods/Design:**

We designed a randomized controlled trial to examine the (cost-) effectiveness of the Kopstoring intervention. Kopstoring is an online intervention for COPMI-children to strengthen their coping skills and prevent behavioral and psychological problems. We will compare the Kopstoring intervention with (waiting list) care as usual. This trial will be conducted entirely over the internet. An economic evaluation, from a societal perspective will be conducted, to examine the trial's cost-effectiveness. Power calculations show that 214 participants are needed, aged 16-25. Possible participants will be recruited via media announcements and banners on the internet. After screening and completing informed consent procedures, participants will be randomized. The main outcome is internalizing and externalizing symptoms as measured by the Youth Self Report. For the economic evaluation, healthcare costs and costs outside the healthcare sector will be measured at the same time as the clinical measures, at baseline, 3, 6 and 9 months. An extended measure for the intervention group will be provided at 12 months, to examine the long-term effects. In addition, a process evaluation will be conducted.

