### Feasibility

Feasibility was a very important key point in writing the proposal for the study. To establish effectiveness 214 respondents are needed. To ensure we could recruit sufficient young people we devised a PR-strategy including high quality advertisements. Links banners and other methods for reaching the target population, will be used. A special budget has been reserved for this purpose.

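### The enrolment target is a division error: 156/(1-0.28) is 216.7, so 217 (218 for equal arms), not 214

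*Protocol article*

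**What the plan says.** The Sample Size calculation section of the protocol article sets out its derivation in full.

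- Effect size: "This corresponds to a standardized mean difference (Cohen's d) of d > 0.45".
- Error rates: "conventional power of (1 - beta) = 0.80 and alpha = 0.05, 2-tailed".
- Number required before drop-out: "For this n = 78 is required per condition, therefore a total of 156 participants".
- Reason for the inflation: "Finally we want to compensate for possible drop-out during the trial".
- Drop-out rate: "The drop-out rate from the pilot study was 28" per cent.
- Result: "We therefore need to enrol 156/(1-0.28) = 214 participants during the trial".

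The target then appears twice more without its derivation. The Methods/Design part of the abstract says "Power calculations show that 214 participants are needed, aged 16-25", and the Feasibility section says "To establish effectiveness 214 respondents are needed".

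**The concern.** The section prints both the formula and its inputs, so the result can be checked directly, and the two sides of the printed equation are not equal. The error also runs in the unfavourable direction. The inflation is there so that enough participants remain after drop-out, yet at the plan's own drop-out rate the printed target is expected to leave fewer than the plan's own requirement.

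The number at stake is the trial's headline size. The abstract attributes it to the power calculation, and a reader of the abstract or the Feasibility section cannot see that the calculation does not produce it. Recruitment will presumably be judged against it.

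**Working it through.** **Inputs**, all from the Sample Size calculation section: d = 0.45; power 0.80; two-sided alpha 0.05; 78 per condition and 156 in total; drop-out 28%.

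**Step 1: reproduce the number per arm.** For two means with equal arms, by the normal approximation:

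n per arm = 2 × (1.96 + 0.8416)² / 0.45² = 77.52, rounded up to 78, so 156 in total.

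This matches the plan exactly. The fault is therefore confined to the drop-out step.

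**Step 2: the inflation as printed.**

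156 / (1 − 0.28) = 156 / 0.72 = 216.67, rounded up to 217.

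Rounding up within each arm: 78 / 0.72 = 108.33, rounded up to 109, so 218 in total.

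The plan states 214. The gap is 3 participants (3/214 = 1.4%), or 4 with equal arms (4/214 = 1.9%).

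**Step 3: could another route give 214?**

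| Route | Total |
|---|---|
| Multiply instead of divide: 156 × 1.28 | 199.7, so 200 |
| Use n per arm before rounding: 2 × 77.52 / 0.72 | 215.3 |
| Drop-out of 27.5%, the lowest rate that rounds to 28%: 156 / 0.725 | 215.2 |
| Round up within each arm: 2 × 109 | 218 |
| Different drop-out: 156 / 0.73 | 213.7 |
| Different starting total: 154 / 0.72 | 213.9 |

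Only the last two give 214 after rounding, and each needs an input that the article does not state (27% drop-out, or 154 participants).

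**Step 4: what 214 delivers.**

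- Expected to remain at 28% drop-out: 214 × 0.72 = 154.1, about 77 per arm and 2 short of 156.
- By comparison, 217 × 0.72 = 156.2 and 218 × 0.72 = 157.0.
- Largest drop-out rate at which 214 still leaves 156: 1 − 156/214 = 27.1%.

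**Step 5: the cost in power for d = 0.45.**

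| Remaining per arm | Normal approximation | t test |
|---|---|---|
| 78 (the plan's requirement) | 80.2% | 79.7% |
| 77 (expected from 214) | 79.7% | 79.2% |

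By either method the slip costs about 0.5 percentage points.

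**The case against.** The strongest reply is that the error has almost no consequence. Power of 79.7% still rounds to 80%. The effect size is a convention, the 28% comes from one pilot study, and uncertainty in either far exceeds 3 participants. This stands as a statement about size.

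Three further points deserve weight.

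- The shortfall is in expectation only. If participants drop out independently with probability 0.28, the number remaining from 214 has a standard deviation of √(214 × 0.28 × 0.72) = 6.6. The chance that fewer than 156 remain is about 58% with 214 enrolled and still about 45% with 217. The correction shifts the odds and guarantees nothing.
- The Analyses section plans intention-to-treat with multiple imputation of completely missing measurements, so the analysis is not confined to those who remain. But the plan sized the trial on the number remaining after drop-out, and imputation neither fully restores lost information nor makes the printed division correct.
- There is one slip, not three. The abstract and the Feasibility section repeat its result and contain no arithmetic of their own. They still need changing if the target changes.

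None of this makes 214 the result of the printed formula.

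**Conclusion.** The concern holds. The printed equation is false: with the plan's own inputs the enrolment target is 217, or 218 with equal arms. Enrolling 214 is expected to leave about 154 participants against the required 156.

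The size is small: 3 to 4 participants (1.4% to 1.9%) and about half a percentage point of power. The trial is not materially underpowered by this. The correction is worth making because the target is the trial's headline number and should follow from the calculation given for it.

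The conclusion takes the plan's d, alpha, power and drop-out rate as given, and assumes 1:1 allocation, which the equal numbers per condition imply.

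**What to change.** Choose one of two corrections and apply it consistently.

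1. **Correct the target.** Replace 214 with 217, or with 218 (109 per arm) for equal allocation, in the Sample Size calculation section, the abstract and the Feasibility section. The cost is at most 4 more online participants.
2. **Keep 214 and correct its justification.** In the Sample Size calculation section, remove the false equality. State either that 214 allows for about 27% drop-out, or that at 28% it leaves an expected 154 participants (77 per arm) with 79.7% power for d = 0.45. The 79.7% rests on the normal approximation, which yields the plan's 78 per arm. If the t-test figure of 79.2% is given instead, name the method and give its comparator at 78 per arm (79.7%), so that the change of method is not mistaken for a loss from the smaller number. The cost is a text change only, and the 214 in the abstract and the Feasibility section can then stay.

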### Cost and outcome measurement

#### I) Effectiveness study

Clinical outcomes will be measured using various questionnaires. The primary outcome of the clinical effect study is the symptoms, complaints and well-being of the young person measured with three questionnaires, each focussing on a different aspect of symptoms, complaints and well-being.

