### Analyses

Data will be analysed according to the intention-to-treat principle, which means including data from all participants irregardless of whether they received the intervention or not. Missing data on the item level will be handled using SPSS missing values analysis. Completely missing measurements will be handled using multiple imputation. A baseline analysis will be performed to examine the comparability of groups at baseline for both costs and outcomes. Differences in baseline will be controlled using applied methods to correct these differences [31]. Losses to follow-up will be described.

The analysis consists of comparing the assessments and scores of the respondents on the questionnaires. Clinical outcomes after the intervention (8 weeks), at three months, six months and twelve months will be compared between groups and within groups, which means we want to compare the effect of the intervention in respondents in the intervention and control groups and assess the additional effects before and after receiving the intervention.

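### The primary outcome is defined in two incompatible ways and no primary time point is fixed for effectiveness, so the stated alpha of 0.05 and power of 0.80 are assured only for each single test.

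*Protocol article*

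**What the plan says.** The Abstract (Methods/Design) of the Protocol article states: "The main outcome is internalizing and externalizing symptoms as measured by the Youth Self Report". Under Cost and outcome measurement, I) Effectiveness study, the text reads: "The primary outcome of the clinical effect study is the symptoms, complaints and well-being of the young person measured with three questionnaires".

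Four instruments are then described. The YSR comes first. Next is the heading Secondary clinical outcome, which introduces the Effect Evaluation List (EEVL). The EQ-5D and the SCL-90 follow under headings of their own.

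On timing, the Analyses section says: "Clinical outcomes after the intervention (8 weeks), at three months, six months and twelve months will be compared", both between and within groups. The Design section measures both arms only at baseline, 3 and 6 months, with 12 months in the intervention arm alone. The Abstract lists 3, 6 and 9 months after baseline. Six months is singled out only for the economic evaluation.

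The Sample Size calculation names neither an outcome nor a time point. It says: "We will test the hypotheses at a conventional power of (1 - beta) = 0.80 and alpha = 0.05, 2-tailed". It takes d = 0.45 and concludes that "n = 78 is required per condition, therefore a total of 156 participants".

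**The concern.** Both definitions of the primary outcome are current text, and both cannot be true. One rests on a single instrument, the other on three. The three are also not clearly identified: only the YSR stands before the heading for secondary outcomes, and the text does not say whether the EQ-5D and SCL-90 belong under that heading.

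Even the Abstract's version leaves choices open. It names two symptom domains without saying whether they form one score or two, and it fixes no visit.

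The trial's main question therefore has no single designated result. At the end, several comparisons could each be presented as primary with some support from the article. A sample size built for one test at 0.05 does not say what the overall error rate or power of that set would be.

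**Working it through.** **Inputs.** From Sample Size calculation: d = 0.45 (SD = 1), two-sided alpha 0.05, power 0.80, 78 per arm, 28% drop-out, 214 to enrol. From Design: both arms are measured after baseline at 3 and 6 months. The number of primary tests (k) and their correlation (r) are not in the document and are assumed below.

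**1. The plan's own figure.** n per arm = 2 × (1.960 + 0.842)² / 0.45² = 77.5, rounded up to 78. At 78 per arm the expected z is 0.45 / √(2/78) = 2.81, and power = Φ(2.81 − 1.96) = 0.802. The t-test version gives 0.797. So 78 is the size for one unadjusted two-sided test, with no allowance for a second.

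**2. Any success counts, each test at 0.05.** For independent tests the family-wise error is 1 − 0.95^k. The correlated ranges come from 400,000 simulated sets of equally correlated normal statistics.

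| Tests | Independent | r = 0.8 to 0.3 |
|---|---|---|
| k = 2 (two YSR domains, or one score at two visits) | 1 − 0.95² = 9.8% | 7.8-9.5% |
| k = 3 (three questionnaires, one visit) | 1 − 0.95³ = 14.3% | 9.8-13.7% |
| k = 6 (three questionnaires at 3 and 6 months) | 1 − 0.95⁶ = 26.5% | 13.9-24.2% |

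Power of each single test stays at 0.80 under this rule.

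**3. Alpha split by Bonferroni.** Power per test at 78 per arm is Φ(2.81 − z), where z is the two-sided critical value for 0.05/k.
- k = 2: alpha 0.025, z = 2.241, power 0.715 (t-test 0.707). Restoring 0.80 needs 94 per arm, and 188/0.72 gives 262 enrolled.
- k = 3: alpha 0.0167, z = 2.394, power 0.661 (t-test 0.652). Restoring 0.80 needs 104 per arm, and 208/0.72 gives 289 enrolled.

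The family-wise error is held at 5% under this rule.

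**4. All tests must succeed, each with true d = 0.45.** Joint power at 78 per arm, for r from 0 to 0.8, is 0.65-0.73 for two tests and 0.52-0.69 for three. The error rate is again not inflated.

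**5. One score at one visit.** Step 1 applies unchanged: 78 per arm, power 0.80.

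**The case against.** The strongest reply is that the figures in the plan are correct as far as they go. The sample size section speaks of hypotheses in the plural, each tested at 0.05, and as a per-test statement both 0.05 and 0.80 reproduce. The article states no rule by which any one positive result wins. Multiplicity rules and testing order are commonly left to a statistical analysis plan, which is not shown here. All of this stands, and the absence of a multiplicity rule is not the finding.

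A reader might infer that the error rate and the power both fail. The documents do not support that. Inflated error arises if every test is run at 0.05 and any success counts. Lower power arises if alpha is split or all tests must succeed. The two penalties belong to different decision rules and cannot be added.

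A reader might also count three questionnaires at three visits and arrive at 1 − 0.95⁹ = 37%. The Design section has only two follow-up visits in both arms. The 8-week point appears only in Analyses and the 9-month point only in the Abstract, while 12 months is intervention arm only. Independence is also unlikely for repeated self-reports from the same person.

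Two smaller points also have force. The three questionnaires could be read as YSR, EQ-5D and SCL-90, with only the EEVL secondary, but the text does not say so. The YSR could also be meant as one score: Target population gives one cutoff per sex, and the cost-effectiveness ratio is expressed per YSR point. The two-test figures therefore depend on how the YSR is scored or on how many visits count.

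None of this removes the contradiction. An analysis plan could choose one of the two published definitions, but it could not honour both.

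**Conclusion.** The point holds in a conditional form. That the primary outcome has two incompatible definitions, and that effectiveness has no primary time point, can be read directly from the article and needs no assumption. The stated alpha and power are assured per test only.

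The size of the consequence depends on a decision rule, a number of tests and a correlation that the document does not give. If any unadjusted success counted, the overall error would be about 8% to 27% across two to six tests and the correlations considered. If alpha were split, per-test power would be about 71% or 65-66% against the stated 80%. These are alternatives, not joint effects.

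The point should be settled before analysis, because it decides which result answers the trial's main question.

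**What to change.** In I) Effectiveness study, replace the three-questionnaire statement with one primary endpoint that agrees with the Abstract: the between-arm difference in one specified YSR score at one specified time point, tested at two-sided 0.05. Six months is the natural choice. Both arms are measured then, and the economic evaluation already takes its effects at that visit and expresses its ratio per YSR point. State exactly how the score is formed. Name the same outcome and visit in Sample Size calculation, and label the other YSR scales, the EEVL, EQ-5D, SCL-90 and all other time points secondary.

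No participants are added, since 78 per arm and 80% power then stand. Choosing the score and the visit is a real design decision for the sponsor, though a small one. The downside is that the other questionnaires can no longer support a primary claim.

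If more than one primary score is kept, state a multiplicity rule such as Holm and restate the power. On the Bonferroni figures above, two primary tests would need about 262 enrolled, against the planned 214, to keep 80% each.

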### Youth Self Report List (YSR) of the Children Behaviour Checklist

The Youth Self Report List will be used to measure each subject's competencies and behavioural problems. The instrument is proven to be valid and has a good internal consistency [20,21]. The Youth Self Report List (YSR) is part of the Child Behaviour Checklist which is a questionnaire measuring internalizing and externalizing psychological problems in young people [20,21]. The Self-Report List has three versions: one each for parents, teachers and young people. For this study we use the young person's version.

### Secondary clinical outcome

The Effect Evaluation List (EEVL) is a Dutch questionnaire tailor-made for the online Kopstoring program: it measures several aspects of coping skills and functioning. The instrument consists of 8 items in two main dimensions: biographical information about the respondent (19 items) and the effect of the COPMI intervention (61 Items). The EEVL has been proven to be valid and has good reliability [22].

### Quality of Life (EuroQol 5D)

The EQ-5D is a self-administered questionnaire. Both generic quality of life, as well as utilities, will be derived by means of the EQ-5D, which will be completed by the young people. The EQ-5D has been chosen because it is a widely used quality of life instrument (nationally and internationally) and its reliability and validity is well established [23]. The EQ-5D contains 5 dimensions of health-related quality of life: mobility, self-care, daily activities, pain/discomfort and depression/anxiety. Each dimension can be rated on three levels: no problems, some problems and major problems. In addition, the EQ-5D consists of a visual analogue scale (VAS) ranging from zero (worst imaginable health state) to 100 (best imaginable health state).

### Utilities

Utilities will be derived from the EQ-5D using the following steps. The 5 dimensions will be summarized into a health state. Utility values will be calculated for these health states, using preferences elicited from a general population, the so-called algorithms. One algorithm has been established using a general population from the UK, the Dolan tariff [24]. For the sensitivity analysis the Dutch algorithm will be used [25]. The utility values derived will be used to compute Quality Adjusted Life Years (QALYs). A QALY combines survival and utilities. The utilities at the three time points will be used to compute the Quality Adjusted Life Years gained (QALY) using of the area under the curve method.

### Symptom Checklist (SCL-90)

The Symptom Checklist has 90 items, each answered using 5 options covering 8 dimensions. These dimensions are: phobia, anxiety, depression, physical complaints, insufficient acting and thinking, distrust and interpersonal sensitivity, hostility and sleeping problems. The SCL-90 is a psychopathology-indicator and covers both somatic and psychological symptoms. It takes about 20 minutes to complete and has been tested and appears to be a valid instrument [26].

#### II) Economic evaluation study

In this economic evaluation we collect data on service use to derive the costs of using these services.

Collecting data on service use:

##### Resource use questionnaire

The use of the Kopstoring program will be measured as well as the use of other resources both within and outside the healthcare sector. A questionnaire will be developed to measure the use of resources.

